#### Missing data

Children with no measure of the primary endpoint will be considered failures regardless of their randomization group. Given the composition of the primary endpoint and the usual practices in the French maternity hospitals, we think that the rate of missing data will be extremely low.

Additional analyzes will be performed on available data and after multiple imputations of missing data.

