### Oxytocin infusion protocol and randomization

During the latent phase, oxytocin is administered according to national guidelines, i.e. low dose oxytocin infusion of less than 4 mUI/min with increments every 30 min, without exceeding a 20 mUI/min flow rate [9].

Women are included and randomized in two groups before 6 cm, during the latent phase (Supplementary Material 1):
The experimental group corresponds to discontinuation of oxytocin at the beginning of the active phase of the 1st stage of labor, i.e. oxytocin infusion is stopped beyond a cervical dilation equal or greater than 6 cm. In the experimental group, oxytocin can be re-started, if necessary, after 2 h of labor arrest (no progression of the cervical dilation and no progression of the fetal head).The control group corresponds to the standard care in France, i.e. when oxytocin is started during the latent phase of the 1st stage administration of oxytocin is continued during the active 1st stage and during the 2nd stage if the fetal heart rate is reassuring. As in French standard practice, the oxytocin infusion is maintained with no increments if cervical dilation progresses. If needed (abnormal fetal heart rate, uterine hyperstimulation) the infusion can be stopped.

The randomization is computerized and accessible 24 h on line. Subjects are distributed between the two groups at a ratio of 1:1. The randomization is stratified on the center and parity (nullipara/multipara). The stratification by center will allow considering the possible variations of practices between centers during labor or delivery (e.g. modalities of epidural analgesia, type of analgesic products used, etc.). Specific information on the practices is also collected in the electronic case report form (e-CRF). The stratification by parity is needed because multiparous and nulliparous women differ on several secondary endpoints such as duration of labor and mode of delivery.

Among women included in the STOPOXY trial, some will have a spontaneous labor and others an induction of labor including induction by oxytocin only or cervical ripening. Induction protocols and particularly cervical ripening methods (Prostaglandins E1, Prostaglandins E2, and mechanical methods) could differ between centers but this potential difference will be taken into account by the stratification by center.

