### Power calculation

A prospective population-based cohort study was conducted in France in 2015 assessing French practices of induction of labor, MEDIP (MEthodes de Déclenchement et Issues Périnatales) [19]. In this study, data on oxytocin use and neonatal outcomes is available. In the French MEDIP cohort, among women receiving oxytocin under standard care (as in our control group), 8% of neonates had at least one criterion of the primary endpoint of STOPOXY trial.

We hypothesize a decrease from 8% with standard care (i.e. control group) to 5% with discontinuation of oxytocin (i.e. experimental group). Assuming this decrease, we need a sample size of 1125 women in each group, for a power of 80% and an alpha risk of 5% with the use of a bilateral test. Because some women could be included and randomized, but never reach 6 cm of cervical dilation, and thus not receive the intervention, we plan to include 10% more women. We suppose that this number will correspond to the number of women having a cesarean delivery before starting the intervention, i.e. before 6 cm. Therefore, to reach statistical significance, we would like to include 2475 women in our trial.

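### Scoring a child with no primary-endpoint measure as a morbidity event is not conservative for an outcome expected at 5–8%; the planned multiple imputation should be primary and the composite's missingness defined

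*Protocol article*

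**What the plan says.** The Missing data section of the protocol article sets one rule for the primary endpoint: "Children with no measure of the primary endpoint will be considered failures regardless of their randomization group". Failure here can only mean that the child is counted as having neonatal morbidity. The section then expects little use of the rule, on the grounds of how the endpoint is composed and of usual French practice: "we think that the rate of missing data will be extremely low". It gives no figure. It closes with "Additional analyzes will be performed on available data and after multiple imputations of missing data", so the two alternatives are planned but do not carry the main result.

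Under Objectives and endpoints, the composite has five components: cord arterial pH, base excess, lactates, 5-minute Apgar score and NICU admission. Under Analysis of the primary endpoint, all randomized women are analysed by intention to treat with a chi-square test. Under Power calculation, the planned rates are 8% and 5%, and the stated requirement is 1125 per group for 80% power at a two-sided 5% level. The total of 2475 comes from a 10% increase, which is there for women who never reach 6 cm and not for missing outcomes.

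**The concern.** Counting missing as failure is usually defended as cautious. That defence suits an endpoint where failure is common, or where only the experimental arm is penalised. Here failure is an uncommon adverse event, and a missing child is given a risk of 100% against a planned 8% or 5%, that is 12.5 or 20 times the planned rate. Each such child adds an event that carries no information about treatment.

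Three things are at stake:
- **Equal missingness.** Uninformative events dilute the risk ratio and raise the variance, so power falls.
- **Unequal missingness.** The gap in missing rates goes almost one for one into the gap in event rates, in whichever direction it happens to run.
- **Unclear scope.** The rule does not say whether a baby with an Apgar score and a known admission status, but no cord result, has a measure of the endpoint. Three of the five components come from the cord sample, so this decides how often the rule bites.

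**Working it through.** **Inputs from the document.** Rates 8% (control) and 5% (experimental); two-sided alpha 5%; power 80%; 1125 per group; total 2475 allocated 1:1, so 2475 / 2 = 1237.5 per arm; chi-square test.

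**Assumed input.** The missing fraction m. The document gives none, so a range of 0 to 5% is shown. Missingness is taken as independent of outcome.

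**Reproducing the plan's figure.** The two-proportion formula without continuity correction gives 1059 per group. With the continuity correction it gives 1125, which matches. Then 2 × 1125 × 1.10 = 2475, which also matches.

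**Equal missingness.** Under the rule, the counted event rate in an arm with true rate p is q = p + (1 − p)m.
- At m = 1%: control 0.08 + 0.92 × 0.01 = 8.92%; experimental 0.05 + 0.95 × 0.01 = 5.95%. Difference 2.97 points, risk ratio 0.667.
- At m = 5%: 12.60% and 9.75%. Difference 2.85 points, risk ratio 0.774.
- With none missing: difference 3 points, risk ratio 0.625.

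Power = Φ[(d − 1.96 × s0) / s1], where d is the difference in q, s0 the pooled standard error and s1 the unpooled one (chi-square without continuity correction). For m = 1% and 1237.5 per arm: d = 0.0297, s0 = 0.010546, s1 = 0.010530, so Φ(0.858) = 80.4%.

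| Missing in both arms | Power, 1237.5 per arm | Power, 1125 per arm |
|---|---|---|
| 0% | 85.7% | 82.3% |
| 0.5% | 83.1% | 79.4% |
| 1% | 80.4% | 76.6% |
| 2% | 75.2% | 71.2% |
| 3% | 70.3% | 66.1% |
| 5% | 61.4% | 57.4% |

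At 5% missing, an available-data analysis keeps 83.9% (1237.5 per arm) or 80.4% (1125 per arm). Most of the loss therefore comes from the rule, not from the missing data.

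The share of counted events produced by the rule is (1 − p)m / q. At 1% missing this is 0.0092 / 0.0892 = 10% in control and 0.0095 / 0.0595 = 16% in experimental. At 5% it is 37% and 49%.

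With equal m and no true effect, q is the same in both arms, so type I error stays at 5%.

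**Unequal missingness, no true effect** (8% in both arms, 1237.5 per arm):
- 2% against 1% missing: 9.84% against 8.92%; rejection 12.3%.
- 3% against 1% missing: 10.76% against 8.92%; rejection 33.6%.

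**Unequal missingness, true 8% against 5%.** With 1% missing in control and 2% in experimental, the counted rates are 8.92% and 6.90%. Power is 46% at 1237.5 per arm and 43% at 1125.

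**The two readings of the rule.** If a child counts as missing only when all five components are absent, the rule almost never applies, since Apgar score and NICU admission should be known for nearly every baby. A baby without cord results could then be scored as unaffected on three criteria that nobody measured. If a child counts as missing when any component is absent, every baby without a cord result becomes an event, and the table applies with m near the rate of missing cord results.

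**The case against.** The strongest reply is that the rule may hardly ever be used. The section expects very little missing data, and its reason, the composition of the endpoint, fits the reading in which all components must be absent. On that reading the figures above are nearly moot. Even on the other reading, 0.5% missing costs under 3 points of power, and at 1% with full recruitment power is still 80.4%. The available-data and imputation analyses are already promised and would show any distortion. Multiple imputation also has its own assumption, that data are missing at random. All of this stands, and it limits the severity.

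It does not rescue the rule. If missingness is negligible, the rule gains nothing. If it is not, the headline result is the distorted one, and the better analyses are only additional.

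Two stronger readings are tempting. A reader might infer that the rule destroys the trial's power. The document does not support that: a severe loss appears only near 5% missing, a rate it nowhere suggests. A reader might also infer that the rule will manufacture a difference because the trial is open-label. That needs unequal missingness, for which the document offers no evidence. The article argues that open-label bias is low because the components are objective, and it describes monitoring by research staff. Objective measurement does not ensure that a measurement is equally available in both arms, so an imbalance is not excluded. That is as far as the document goes.

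**Conclusion.** The point holds as a weakness in how the primary analysis is fixed, of minor to moderate weight. For an adverse event expected at 5–8%, counting missing as failure is not conservative: it attenuates the risk ratio and lowers power when missingness is equal, and it can bias the comparison either way when it is not. The size rests on an assumed missing rate. At 1237.5 per arm the loss is about 3 points of power at 0.5%, 5 points at 1% and 24 points at 5%. The false-positive figures of about 12% and 34% rest further on an assumed imbalance between arms. Which reading of the rule applies decides whether these figures matter at all, and the article's wording leaves that open.

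**What to change.** Reword the Missing data section before any unblinded look at the data:

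1. Score the composite positive if any observed criterion is met.
2. If no observed criterion is met and the cord results are missing, treat the composite as missing. State whether one of pH, base excess or lactates is enough to count the cord result as present.
3. Make the already planned multiple imputation the primary approach: impute the missing components using arm, center, parity, onset of labor, mode of delivery, Apgar score and admission, then derive the composite.
4. Keep missing = failure and available-data analyses as sensitivity analyses.
5. Report missingness by arm, per component and for the composite.

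The cost is wording and slightly more programming. The primary result would then rest on a missing-at-random assumption, which the retained sensitivity analyses help to probe. Sample size, data collection and conduct do not change.

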#### Analysis of the secondary endpoints

The analysis of the secondary endpoints will be done using the statistical tests adapted to the studied variables. The comparison of two means will be done by Student’s t test or if necessary by Wilcoxon tests. The comparison of percentage will be done using chi-square tests or Fisher’s exact test if necessary. All tests will be bilateral with a significance level of 5%.

#### Subgroup analysis

We plan two subgroup analyses. The first analysis will be done according to the mode of onset of labor: cervical ripening, oxytocin, spontaneous. And the second analysis will be done according to parity.

The center and parity are two criteria used to stratify our randomization. They will therefore be distributed equally among the 20 centers. These two criteria are known to be associated with the use of oxytocin and labor duration which can both play a role on our primary endpoint.

### Methods for monitoring compliance with the treatment

To avoid the contamination between the two groups because of the open-label design, the respect of the allocated group of treatment as well as the total dose and the duration of oxytocin administration will be prospectively and exhaustively monitored by clinical research assistants during the study. In case of deviations from the protocol there will be reminders to the centers and regular checks. The data collection will be performed by clinical study technicians.

## Discussion

### Potential implication of the findings

Improving management of labor represents an opportunity of improving the health of both women and infants. In most women, stopping oxytocin in the active phase may improve fetal tolerance to labor by reducing uterine hypercontractility therefore decreasing fetal heart rate abnormalities. In most severe situations, the discontinuation of oxytocin could reduce severe neonatal morbidity, which may cause neurologic damages, and moderate neonatal morbidity, which may be associated with the need of resuscitation and hospitalization. Unlike previous published studies, the STOPOXY trial, which plans to include a large sample of women, will have sufficient power to demonstrate a difference in neonatal morbidity if it exists.

In addition, we expect that the reduction of neonatal morbidity associated with oxytocin discontinuation will be associated with a reduction in maternal morbidity, in particular due to a reduction of postpartum hemorrhage which remains the leading cause of postpartum maternal morbidity.

The SPIRIT checklist can be found as Supplementary Material 2.

## Data Availability

Not applicable.

## Abbreviations

95% CI: 95% Confidence Interval
CNGOF: Collège National des Gynécologues Obstétriciens Français
GROG: Groupe de Recherche en Obstétrique et Gynécologie
EPDS: Edinburgh Postnatal Depression Scale
e-CRF: Electronic case report form
FHR: Fetal heart rate
LAS: Labor agentry scale
MEDIP: MEthodes de Déclenchement et Issues Périnatales
NICU: Neonatal intensive care unit
PPH: Postpartum hemorrhage
